# Communities in charge of alcohol (CICA): a protocol for a stepped-wedge randomised control trial of an alcohol health champions programme

**DOI:** 10.1186/s12889-018-5410-0

**Published:** 2018-04-19

**Keywords:** Alcohol, Public health, Asset based community development, Brief intervention, Licensing, Dark logic, Community-based prevention

## Abstract

**Background:**

Communities In Charge of Alcohol (CICA) takes an Asset Based Community Development (ABCD) approach to reducing alcohol harm. Through a cascade training model, supported by a designated local co-ordinator, local volunteers are trained to become accredited ‘Alcohol Health Champions’ to provide brief opportunistic advice at an individual level and mobilise action on alcohol availability at a community level. The CICA programme is the first time that a devolved UK region has attempted to coordinate an approach to building health champion capacity, presenting an opportunity to investigate its implementation and impact at scale. This paper describes the protocol for a stepped wedge randomised controlled trial of an Alcohol Health Champions programme in Greater Manchester which aims to strengthen the evidence base of ABCD approaches for health improvement and reducing alcohol-related harm.

**Methods:**

A natural experiment that will examine the effect of CICA on area level alcohol-related hospital admissions, Accident and Emergency attendances, ambulance call outs, street-level crime and anti-social behaviour data. Using a stepped wedged randomised design (whereby the intervention is rolled out sequentially in a randomly assigned order), potential changes in health and criminal justice primary outcomes are analysed using mixed-effects log-rate models, differences-in-differences models and Bayesian structured time series models. An economic evaluation identifies the set-up and running costs of CICA using HM Treasury approved standardised methods and resolves cost-consequences by sector. A process evaluation explores the context, implementation and response to the intervention. Qualitative analyses utilise the Framework method to identify underlying themes.

**Discussion:**

We will investigate: whether training lay people to offer brief advice and take action on licensing decisions has an impact on alcohol-related harm in local areas; the cost-consequences for health and criminal justice sectors, and; mechanisms that influence intervention outcomes. As well as providing evidence for the effectiveness of this intervention to reduce the harm from alcohol, this evaluation will contribute to broader understanding of asset based approaches to improve public health.

**Trial registration:**

ISRCTN 81942890, date of registration 12/09/2017.

## Background

Reducing alcohol related harm continues to be a global public health priority, with 5.9% of all global deaths and 5.1% of all disease and injuries being attributable to alcohol [1]. Excessive alcohol consumption harms an individual’s health and social relationships [2]. It also harms society more generally, as urban areas can become less pleasant and less safe to visit [3] and crime may increase [4]. Moreover, the consumption of alcohol contributes significantly to health inequalities. Those living in deprived areas drink the same average quantity of alcohol as those from more advantaged groups. However, a so-called ‘alcohol harm paradox’ exists whereby, for a given level of alcohol consumption, alcohol harm is higher amongst those living in more deprived areas [5]. Possible reasons for this include patterning of consumption (e.g. consuming the same quantity on fewer occasions [6]) and combinations of other health risks (e.g. smoking, obesity) in individuals living in deprived areas [7]. Interventions that are effective at reducing alcohol harm have been shown to operate at the individual level (i.e. brief advice about drinking [8]), the community level (e.g. licensing policies [9, 10] and measures that control access to alcohol [8]), and national level (e.g. alcohol pricing policy [2]). This protocol describes an evaluation of an intervention, ‘Communities In Charge of Alcohol’ (CICA), which aims to target alcohol harm at two levels; by influencing individuals (through brief intervention) and communities (through reducing the availability of alcohol).

Brief interventions and brief advice have been shown in systematic reviews and meta-analyses to be effective in a variety of settings including emergency departments [11] and primary care [8]. There is relatively little evidence about training lay persons for this role, although pilot work with ex-offenders giving advice to offenders in community settings seems promising [12]. Accessibility of alcohol is a key determinant of harm [5, 13, 14]. Internationally, systematic review evidence shows that high alcohol outlet density is linked to higher levels of crime and poor health [15]. A systematic review (rated high quality [16]) found that higher outlet density and greater exposure to advertising tends to be associated with higher levels of alcohol use [17]. Interventions that change the alcohol environment thus have the strongest evidence for effectiveness [2, 16, 18].

In England, local authorities can address public health through licensing policies. However, because ‘public health’ is not currently one of the licensing objectives, the extent to which this is carried out varies across the country [9]. Local people have the ability to influence the availability of alcohol via the licensing process, but do not tend to do so, due to low awareness and lack of confidence that local views will be valued [19]. Recent longitudinal, area-level analysis of UK datasets shows that, at borough level (i.e. lower tier local authorities in England) both alcohol-related hospital admissions [9] and crime [10] have reduced faster in areas where more restrictive licensing policies are in place. Using small area level data (lower super output areas [LSOA^1^] with a mean population of 1500 persons), alcohol outlet density in Wales is similarly associated with alcohol-related hospital admissions and crime data [5]. The possibility of utilising community advocacy to reduce the availability of alcohol has not been explored but could represent an untapped resource. This aligns to the UK Government’s attempts to make it easier for residents and other local agencies interested in licensing to take action [20].

The CICA programme takes an Asset Based Community Development (ABCD) approach, where a health asset is any factor which enhances the ability to create or sustain health and wellbeing [21]. This is in line with the National Institute for Health and Care Excellence (NICE) guidance on behaviour change, which advocates building on existing community resources and skills [22]. The principles of the approach are to: allow time for communities to realise and acknowledge their individual and collective assets and to rebuild their confidence and networks; enable local people to take the lead, and; build trust with communities by demonstrating that involvement leads to change [23]. The approach seeks to build community networks, which are health promoting [24]. The programme aims to enable local volunteers working with the community to identify alcohol harm in their community, and facilitate them to intervene to reduce these harms.

## Methods/design

The overarching aim of this research is to evaluate the effectiveness of a community Alcohol Health Champions programme (Communities in Charge of Alcohol: CICA) to reduce alcohol-related harm. Secondary aims include determining the cost consequences of CICA and exploring the context, barriers and facilitators to its implementation. As a complex community intervention, it is not amenable to conventional randomisation (as recognised in the complex interventions guidance [25]) and will be evaluated as a natural experiment [26]. This fits on the ‘continuum of evaluation’ [27], which recognises the need for multiple methods/variants on experimental design [28].

Through CICA, individuals embedded within areas identified as having high levels of alcohol-related harm are recruited by local co-ordinators to take part in a 2 day ‘Alcohol Health Champion’ (AHC) course. As a community asset connected to the area either through their residency or their work role, an Alcohol Health Champion’s existing strengths, motivations and skills are strengthened to enable them to (i) give alcohol-related brief advice to others and (ii) tackle the availability of alcohol in the local environment through the licensing process. Using a cascade training model, an accredited and standardised training course is delivered initially by the Royal Society for Public Health (RSPH) and then cascaded by the Alcohol Health Champion community with the support of professionals. This community hub approach means that AHCs have an infrastructure of support provided by local co-ordinators and local licensing officers. The AHC role description specifies that champions should only do whatever they are comfortable with and that the programme does not dictate where, when or how much activity should take place. This is largely based on the existing health champions model which utilises lay health workers from a variety of backgrounds (e.g. voluntary sector, housing, local residents) to work in a voluntary capacity to offer brief advice and brief interventions alongside their other daily activities [29]. However, for the first time, through CICA, champions will be trained to focus on alcohol and will receive additional knowledge and skills to enable them to get involved in local licensing decisions.

A logic model was created as part of the planning of this evaluation (Fig. 1). This shows the intervention’s mechanisms of action and the interplay between its core components. At the heart of the CICA programme, based on ABCD principles, is the assumption that individuals and communities have strengths, motivations and skills that benefit everyone. Further, there is an assumption that the AHC training programme and infrastructure of support can help build the strengths, motivations and skills of these individuals to develop confidence to put their skills into practice. As communities take action by offering brief advice or getting involved in licensing decisions, a feedback loop illustrates how such success positively reinforces the strengths, motivations, and skills of the community. Influencing access and availability to alcohol and building a groundswell of brief advice about alcohol should, as a result, directly impact on alcohol related outcomes.

**Fig. 1 Fig1:**
[figure not shown]
CICA Evaluation Logic Model

Additionally, we also considered the possible unintended consequences of the intervention (see Fig. 2). Few public health interventions and evaluations explicitly look at unintended harms and, although logic models considering positive consequences and outcomes are common, the consideration of the potential negative outcomes (and their mechanisms of action), or a ‘dark’ logic model, are less common [30]. According to Bonell et al. [31], not only is it important to produce a dark logic model ahead of the evaluation/intervention, or during it, but also the framework could be useful to evaluate the project retrospectively to see how it might have been strengthened. To develop the dark logic model we first created a matrix to hypothesise *a priori* the potential unintended consequences of CICA using a simple framework, adapted from Lorenc and Oliver’s five categories of harm (see Table 1) [30]. Each potential harm was reflected upon using one of three approaches recommended by Bonell et al. [31]: how agencies and structures may interact in unintended ways; comparative understanding across similar interventions; and consultation with individuals/groups with insights into local contexts and how interventions might operate within them. Evidence that supports or refutes the hypothesised unintended consequences of the intervention will benefit future design and minimise the risk of future harm [31].

**Fig. 2 Fig2:**
[figure not shown]
CICA “Dark” Unintended Consequences Logic Model

**Table 1 Tab1:** CICA Matrix of potential unintended consequences

Potential unintended consequences	How agencies and structures may interact in unintended ways	Comparative understanding across similar interventions	Consultation with individuals/groups with insights into local contexts and how interventions might operate within them (CICA Project Advisory Group)
Direct harms	None identified	Lack of depth of knowledge by lay health advisors could result in time delays or inconsistent advice for ‘in-need’ populations [48]	Concerns that volunteers recruited from recovering communities could be at increased risk of relapse of alcohol, drug or mental health problems
Psychological harms	None identified	Volunteers embedded within communities find it hard to ‘switch off’ [48]	Intervening in licensing could lead to negative reactions from local retailers
		Dissatisfaction and disillusionment of volunteers [49]	
Equity harms	Communities most in need are probably the least able to form a strong community group [50, 51]	Motivated individuals becoming health champions are likely to benefit from being a champion more so than those less motivated (who need the potential positive benefits more) [48]	Individual assets within communities excluded from participation due to barriers to recruitment/participation e.g. literacy, criminal record checks, worry about impact on benefits
Group and social harms	‘Communities’ chosen to be in charge of alcohol set by experts (normative needs) vs. self-identified communities (felt needs) [49]	Becoming a community champion could result in lack of acceptance by own community resulting in marginalising “do gooders” [48]	None identified
		Current recovery dominated culture within alcohol service provision in UK influences the selection of volunteers from ‘recovery’ communities [52]	
Opportunity cost harms	Commissioners may miss opportunities to invest in alternative public health interventions [53]	Missed opportunities to identify “at-risk” populations [54] due to stereotyping those ‘in need’ as only the most severe drinking patterns [55]	None identified

### Setting

All Greater Manchester (GM) boroughs within the study setting have higher than England averages for alcohol-related mortality, ranging from 46.7 in Trafford to 71.9 per 100,000 in Manchester [32]. GM is heterogeneous in terms of its application of licensing policy: in a recent national study, only one local authority was classified as having high licensing policy intensity (two local authorities were medium, five low and two passive in terms making use of cumulative impact areas and/or declining licences [9]).

CICA will be rolled out sequentially across specifically targeted areas in all 10 local authorities, with the sequence randomly assigned by the research team, so that it will eventually (within the timespan of a year) be delivered in all areas. The intervention areas themselves within each local authority will be formed around pre-existing communities in LSOA locations. For data analysis purposes, the chosen LSOAs that represent each community combine to make the ‘intervention area’ unit of analysis. For example, the smallest intervention area encompasses one LSOA (mid-year population estimate of 1648) and the largest contains three LSOAs (mid-year population estimate combined of 5586).

### Characteristics of study population

In order to ensure there is consistency for the evaluation, each local authority used the following guiding principles as inclusion criteria for selecting an intervention area dependent on local available data:An area of high alcohol-related harm (defined as high within the local authority, rather than in comparison to regional or national average rates)Alcohol harm considered in terms of a combination of indicators:Alcohol-related crime^2^ and anti-social behaviour (ASB)^3^Alcohol-related hospital admissionsWeekend evening Accident and Emergency (A&E) attendancesUsers of local treatment servicesHospital recording of location of violent incidents (if available)Density of licensed premises in the area or adjoining areas (if available)

The study population of AHCs will include adults aged 18 years and over, who are already embedded in the intervention area either through their residency or their work role (i.e. they must spend the majority of their time in the intervention area).

### Outcome evaluation

The effectiveness of CICA will be measured through the following data and objectives:Routinely collected quantitative data to determine the effect on key health performance indicators (narrow indicator of alcohol-related hospital admissions,^4^ A&E attendances and ambulance call-outs);Routinely collected street-level crime data to determine the effect on key crime indicators;Routinely collected anti-social behaviour data to determine the effect on key ASB indicators.

The aims and objectives of the outcome evaluation will be reached through outcome analysis at the level of the small intervention area (the equivalent of one to three LSOAs) comparing areas where CICA has not yet been introduced. The outcome analysis involves two distinct approaches:***‘Internal’ evaluation***: Trends in area-time intervention areas will be compared before and after the intervention using a stepped-wedge randomised trial design [33]. Sensitivity analyses using different lagging periods (6–24 months) between introduction of the intervention and expected effects will allow for a delayed effect on output measures. If differences in the slopes of the longitudinal models are observed, the population impact will be estimated from deviation of the post-intervention slope compared to the pre-intervention slope.***‘External’ evaluation***: Secondly, the impact of the intervention will be assessed using two complementary methods: (i) matching intervention and control areas inside the GM area by area-level deprivation, population size, age distribution and baseline alcohol-related burden by calculating propensity scores [34]. Temporal trends in each of the outcomes will be plotted graphically and analysed using hierarchical growth models (similar to de Vocht et al. [9, 10]); and (ii) using time series data from GM LSOAs to construct weighted ‘synthetic control time series’ [35] that mimic the ‘intervention area’ as closely as possible prior to the introduction of CICA. Modelled and measured post-introduction time series will then be compared directly to quantitatively estimate the impact of CICA. Both methodologies (i and ii) are complementary, and while the latter approach has the distinct advantage that it provides a direct comparison to the counterfactual time-series, it can be considered as less insightful than the former method because it does not compare actual areas on the ground.

The external evaluation may be affected by ‘spill-over’. In other words, if, as a result of the introduction of CICA, it becomes more difficult for new premises to obtain a premises licence in the specific intervention areas, these may decide to establish themselves in neighbouring areas (close to the border). Conversely, AHCs could get involved in licensing decisions in these neighbouring areas directly. These are known ‘spill-over’ issues [36], but difficult to tackle, and therefore directly neighbouring LSOAs will not be incorporated into control areas. Instead, only LSOAs that are further away are combined and matched, as outlined above, using propensity score matching or incorporated in the synthetic control time series.

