### Statistical analysis and power calculation

Statistical power calculations were based on the methodology for stepped-wedge randomised trials outlined in Hussey and Hughes [33]. These were calculated specifically for the primary outcome ‘alcohol-related hospital admission rates (narrow)’ obtained from the Local Alcohol Profiles for England (LAPE)^4^ extracted for all 10 GM local authorities. Statistical power analyses were conducted at local authority level rather than at the level of the intervention area (the equivalent of one to three LSOAs) because the exact areas and comparisons had not been determined, but this aggregated level provided indications within the stepped wedge context. The mean standardised alcohol-related hospital admission rate in these local authorities for the year 2014 was 207 (per 100,000 people) with a maximum temporal standard deviation per site of 17.2 (range within sites 5–17) and a coefficient of variation across sites of 4.35. With 10 areas and 12 month follow-up (i.e. when all areas have received the intervention and a minimum of 1-month post-intervention follow-up), and a statistical significance level of 5% and statistical power of 90%, the proposed study will be able to detect a 10% average difference in rates compared to baseline. For an intervention to be effective and cost-effective a minimal reduction in key indicators of 10% seems reasonable. Statistical analyses will use standard mixed-effects models with an indicator of when the intervention was introduced in each area and a time component to account for the repeated measures nature of the data.

With respect to the comparison with propensity matched controls and synthetic controls in which time trends will be compared within the larger area of between different areas, no additional clustering occurs. Assuming a standard comparison of independent means, 1-sided test, and significance level of 5%, changes in alcohol-related hospital admission rate in the intervention LSOA, relative to the selected comparison area, yield an 84% statistical power to detect a similar 10% decrease. Trends in matched areas are evaluated using mixed-effects log-rate models as previously used at lower-tier local authority area level for alcohol-related hospital admissions [9] and alcohol-related crime rates [10] in England.

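### The internal evaluation quantifies population impact only if slopes are seen to differ, and as a slope change, which is not reconciled with the intervention-indicator model and the average rate difference that was powered

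*Protocol article*

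**What the plan says.** Three statements in the protocol article bear on how the internal effect is obtained.

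- **Outcome evaluation, design.** "Trends in area-time intervention areas will be compared before and after the intervention using a stepped-wedge randomised trial design [33". The paragraph's opening also refers to "comparing areas where CICA has not yet been introduced". The randomised element, under Setting, is the order of roll-out: "with the sequence randomly assigned by the research team".
- **Outcome evaluation, impact rule.** "If differences in the slopes of the longitudinal models are observed, the population impact will be estimated from deviation of the post-intervention slope", the reference being the slope before the intervention. This is the only sentence that says how population impact is derived in the internal evaluation.
- **Statistical analysis and power calculation.** "Statistical analyses will use standard mixed-effects models with an indicator of when the intervention was introduced in each area and a time component". The reason given for the time term is "a time component to account for the repeated measures nature of the data"; secular trend and season are not mentioned. The power statement is for a 10% average difference in rates against baseline (10 areas, 12 months, 5% significance, 90% power).

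Under Characteristics of study population, areas were chosen on this principle among others: "An area of high alcohol-related harm (defined as high within the local authority, rather than in comparison to regional or national average rates".

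**The concern.** The impact rule raises three problems.

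1. **It depends on the data.** An estimate that is produced only when a difference is seen is, on average, too large when power is low.
2. **It is a different quantity from the one powered.** The power calculation concerns a shift in the average rate. The rule reports a change in slope. An effect of the planned kind need not change the slope at all.
3. **It names no concurrent comparison.** Random ordering protects the contrast between exposed and not-yet-exposed areas in the same calendar period. Post-slope minus pre-slope draws on that contrast only if the model takes out calendar time flexibly. Roll-out is completed within a year, so exposure and season overlap, and areas chosen for high harm may drift down together afterwards.

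At stake is the headline figure for the internal evaluation: it could be missing when a real level effect exists, too large when it does appear, or partly a calendar effect.

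**Working it through.** **1. The plan's own figure, and the quantity it refers to.** Mean rate 207 per 100,000, so the target is 0.10 × 207 = 20.7. The largest temporal SD is 17.2. In the Hussey-Hughes calculation, power = Φ(20.7/SE − 1.96), where SE is that of the step term with area and period effects. With ten single-area steps and 11 or 12 periods, SE is 5.13 to 5.73 over three readings of the stated coefficient of variation (4.35%, 0.435, 4.35):

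- 20.7/5.13 − 1.96 = 2.07, power 98%
- 20.7/5.73 − 1.96 = 1.65, power 95%

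Five steps give 74% to 83% two-sided. The number of steps, sidedness and unit of the coefficient of variation are not stated, so 90% can be neither confirmed nor called wrong. What matters here is that the calculation is for a step (level) term, not a slope change.

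**2. Estimating only when a difference is seen.** Assume *observed* means two-sided p < 0.05. Let λ = true effect/SE. Ignoring the wrong-sign tail, λ = 1.96 + Φ⁻¹(power), and the mean significant estimate divided by the truth is 1 + φ(1.96 − λ)/(power × λ).

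| Power | λ | Ratio |
|---|---|---|
| 90% | 3.24 | 1 + 0.1755/(0.9 × 3.24) = 1.06 |
| 50% | 1.96 | 1 + 0.3989/(0.5 × 1.96) = 1.41 |
| 20% | 1.12 | 1 + 0.2800/(0.2 × 1.118) = 2.25; 2.23 with the wrong-sign tail included |

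The range is shown because the protocol worked out power at local-authority level, while analysis is at the level of intervention areas with populations of 1,648 to 5,586. Power at that level is not given.

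**3. Slope change against level effect.** Simulation with assumed layout: 10 areas, 36 monthly points, SD 17.2, one area entering per month after about two years of prior data. The true effect is a level drop of 20.7 with no trend.

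- Area + period + step: mean estimate −20.7, rejection 99.6%.
- Area + linear time + step + post-introduction slope, reading the slope term: mean 0.00, rejection 4.6%.

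When both terms are in the model, the step takes up the level effect and the slope change shows nothing. The condition for estimating impact would then usually not be met.

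**4. Calendar time.** Same layout, no true effect:

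- Common straight-line trend, linear-time model: slope term rejected 5.2% of the time, so no bias.
- Common trend that bends by −1 per month at roll-out, linear-time model: mean slope change −0.59, rejection 11.1%.
- Same bend, period effects: slope term −0.02 (5.4%), step term 0.02 (5.4%).

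For season, assume a common cosine of ±10% and a model with area intercepts, linear time and a time-since-introduction slope, one area per month. At the worst phase the spurious slope change is 0.69% per month with 12 months of prior data and 11 months from the start of roll-out. It falls to 0.15% per month when the series runs 24 months from the start of roll-out, and to zero with period effects. The bias therefore depends on the form of time and the length of series, neither of which the document gives.

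**The case against.** A reader might infer that the internal analysis throws away the randomised contrast, or that the effect is estimated only if slopes differ. The document does not support that. It places the internal evaluation in a stepped-wedge design with areas not yet exposed as comparators, and the indicator-plus-time model carries no condition. The condition attaches to the population-impact quantity alone. This stands.

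A reader might also infer that calendar-time bias and regression to the mean are built in. They are not. A time term adjusts for time whatever reason is given for it, and its form may be left to the analysis plan. All areas were chosen on similar principles and the order is random, so a common fall after selection is calendar time, which period effects remove. Nor can the fall be sized: selection used several indicators as guiding principles, with no single year or ranking stated. This stands too.

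Three further inferences go beyond the text:

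- That null results will be withheld. The sentence says *observed*, not significant, and nothing says that other results go unreported.
- That no post-slope can be fitted in the last area. The one-month minimum is a premise of the power calculation, not a data cut-off. Lags of 6 to 24 months are planned, and a mixed model pools slopes across areas.
- That the slope rule feeds the costs. The economic section says that it follows the outcome-analysis methods, but it names the log-rate, differences-in-differences and Bayesian structural time series models, not this rule.

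At the stated 90% power the overstatement is only 6%. That is a fair limit if that power applies to the small areas.

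None of this reconciles the impact sentence with the model and the powered quantity.

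**Conclusion.** The point holds as a defect in one stated rule. The protocol has two unreconciled routes to the internal effect: an unconditional indicator model matched to the power calculation, and a conditional slope change called population impact.

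- **Overstatement:** about 1.06-fold at 90% power, 1.4-fold at 50% and 2.2-fold at 20%, if *observed* means significant.
- **Missed effect:** a pure level drop of the powered size leaves the slope term at its null rejection rate (4.6%, against 99.6% for the step term) when the model holds both. This rests on the assumed layout and on the local-authority SD of 17.2.
- **Calendar bias:** possible only if time is modelled too simply, for instance as linear when the trend bends or is seasonal. It vanishes with period effects. Its size cannot be fixed from the document, and the figures above only illustrate the dependence.

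The correction should be made before outcome data are analysed. It does not call the stepped-wedge design itself into question.

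**What to change.** Delete the conditional slope sentence. State instead that the intervention effect and its 95% CI will always be reported from the stepped-wedge mixed model with area effects and categorical calendar-period effects, on the powered scale (average rate difference, or the equivalent rate ratio), whether or not slopes differ. Describe the time component as adjusting for calendar time as well as repeated measures. Any slope change or time-since-introduction effect should be a secondary estimate from the same model with period effects, also reported regardless of its result.

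The cost is a change of wording and a few degrees of freedom for the period effects. No new data are needed.
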